## Abstract

**Background:**

Intraoperative and postoperative management of cardiac surgery patients is complex, involving the application of differential vasopressors and volume therapy. It has been shown that a positive fluid balance has a major impact on postoperative outcome. Today, the advantages and disadvantages of buffered crystalloid solutes are a topic of controversy, with no consensus being reached so far. The use of hypertonic saline (HS) has shown promising results with respect to lower total fluid balance and postoperative weight gain in critically ill patients in preliminary studies. However, collection of more data on HS in critically ill patients seems warranted. This preliminary study aims to investigate whether fluid resuscitation using HS in patients following cardiac surgery results in less total fluid volume being administered.

**Methods:**

In a prospective double-blind randomised controlled clinical trial, we aim to recruit 96 patients undergoing elective cardiac surgery for ischaemic and/or valvular heart disease. After postoperative admission to the intensive care unit (ICU), patients will be randomly assigned to receive 5 ml/kg ideal body weight HS (7.3% NaCl) or normal saline (NS, 0.9% NaCl) infused within 60 min. Blood and urine samples will be collected preoperatively and postoperatively up to day 6 to assess changes in renal, cardiac, inflammatory, acid-base, and electrolyte parameters. Additionally, we will perform renal ultrasonography studies to assess renal blood flow before, during, and after infusion, and we will measure total body water using preoperative and postoperative body composition analysis (bioimpedance). Patients will be followed up for 90 days.

**Discussion:**

The key objective of this study is to assess the cumulative amount of fluid administered in the intervention (HS) group versus control (NS) group during the ICU stay. In this preliminary, prospective, randomised controlled clinical trial we will test the hypothesis that use of HS results in less total fluids infused and less postoperative weight gain when compared to the standard of intensive care in cardiac surgery patients.

**Trial registration:**

ClinicalTrials.gov, NCT03280745. Registered on 12 September 2017.

**Electronic supplementary material:**

The online version of this article (10.1186/s13063-019-3420-6) contains supplementary material, which is available to authorized users.

## Background

Cardiovascular surgery for ischaemic or valvular heart disease has become a major approach in daily practice in industrialised countries, with more than 100,000 surgeries performed in Germany per year [1]. Perioperative management of cardiac surgery patients remains complex; challenges for anaesthesiologists and intensive care physicians arise from specific characteristics of the underlying cardiac disease, the complexity of the surgical intervention, and the pathophysiological impact of extracorporeal circulation [2]. Furthermore, cardiac surgery alters fluid balance significantly, generates a systemic inflammatory response that increases oxygen consumption, and is associated with changes in cardiac output and oxygen delivery [3, 4].

Recommendations for fluid strategies have changed considerably in recent years [1]. Despite the ongoing debate over the role of colloids in patients undergoing cardiac surgery [4–6], growing doubt with regard to the safety and efficiency of colloid solutes has led to increased use of crystalloid solutes [1, 7, 8]. According to a recent large multicentre survey conducted in Germany, crystalloids are considered the fluid of choice for intraoperative fluid therapy, cardiopulmonary bypass circuit priming, and post-surgery intensive care [1].

Critically ill patients, and especially patients undergoing cardiac surgery, receive considerable amounts of intravenously administered fluid [9, 10], which often results in fluid overload. Despite common perception, fluid overload is not a benign occurrence, with mounting data demonstrating an association with prolonged intensive care unit (ICU) and hospital length of stay and increased mortality [11, 12]. In addition, fluid overload (defined as a ≥ 10% increase in body weight) [13] has been associated with increased perioperative complications [14, 15] and decreased gastrointestinal function [9, 16].

Fluid resuscitation using a bolus or continuous infusion of hypertonic saline (HS) has been used for more than 30 years [9, 17, 18]. HS expands intravascular volume by shifting fluid from the extravascular space [19, 20], thus increasing preload [21, 22]. Compared to conventional artificial plasma expanders or human plasma, HS is considered inexpensive, rapidly available, and without risk of anaphylaxis or transmission of infectious disease [22]. Despite potential physiological advantages, HS has been used less in recent years, which may at least partially be due to previous use of mixed solutions (e.g. HS with colloids). Currently, studies assessing the use of HS for fluid resuscitation in critical illness are scarce and heterogeneous regarding effects on clinical outcomes. However, several studies have shown that infusion of HS results in less volume administered [22–26], favourable total fluid balance [22–24, 26], and less weight gain after surgical procedures when compared to normally used crystalloids [23, 27]. Thus, fluid resuscitation with HS infusion may provide benefits in selected critically ill patients. In patients undergoing cardiac surgery, only one study was conducted with the primary outcome of fluid status after surgery [27]. It showed promising results in terms of less total volume infused, less postoperative weight gain, and increased postoperative diuresis. However, these findings await confirmation in a larger population.

We propose a preliminary prospective, single-centre, randomised controlled clinical trial on the use of HS (7.3% NaCl) versus NS (0.9% NaCl) in addition to conventional fluid resuscitation with lactated Ringer’s solution in patients after cardiac surgery. We will test the hypothesis that use of HS results in less total volume infused and less postoperative weight gain when compared to fluid resuscitation with the standard of care in patients after cardiac surgery.

## Objectives

### Primary objective

This preliminary study aims to investigate whether fluid resuscitation using HS in patients following cardiac surgery results in less total fluid volume administered.

### Secondary objectives

Secondary objectives are to investigate whether the use of HS results in less postoperative weight gain, reduced cumulative vasopressor dose and shorter time on vasopressors after cardiac surgery, as well as increased urinary output.

### Exploratory outcomes

Further, we will assess whether use of HS results in a change in acid-base parameters and electrolyte levels as well as inflammatory/immune, cardiac, and renal function indices. Differences in clinical outcome comparators, including body composition analysis (water balance) using bioimpedance, need for renal replacement therapy, time on the ventilator, length of ICU and hospital stay, as well as ICU and in-hospital mortality and 30-day and 90-day mortality, will also be analysed.

## Methods

The “Hypertonic saline for fluid resuscitation after cardiac surgery (HERACLES)” study is a single-centre prospective double-blind randomised controlled clinical trial taking place in a tertiary care university hospital (Department of Intensive Care Medicine, Inselspital, Bern University Hospital, University of Bern, Switzerland). Recruitment started February 27, 2018 (ongoing); the current protocol version is V1.3, dated March 1, 2018.

All patients undergoing cardiac surgery at our institution will be screened according to the predefined inclusion and exclusion criteria before written informed consent is obtained. Prior to enrolment, the investigators will explain to each participant the nature of the study, its purpose, the procedures involved, the expected duration, and the potential risks and benefits. To give consent to participate, the patient and the investigator or his/her designee will sign an informed consent form (ICF). Thereafter, the patient will be enrolled in the study. Study procedures are performed according to the planned schedule with adherence to visit intervals.

A Standard Protocol Items: Recommendations for Interventional Trials (SPIRIT) checklist is provided in Additional file 1. A schedule based on SPIRIT recommendations is shown in Fig. 1.

**Fig. 1 Fig1:**
[figure not shown]
SPIRIT figure indicating visits and study-specific assessments

### Approvals

This study has been approved by the cantonal committee responsible for ethical research in humans (Kantonale Ethikkommission, KEK, Bern, Switzerland, approval number 2017-00647). Written informed consent will be obtained from all participants.

### Population

We aim to include a total of 96 patients (n = 48 per group) undergoing elective cardiac surgery for ischaemic and/or valvular heart disease and receiving the allocated study investigational medicinal product (IMP).

#### Inclusion criteria

Patients aged ≥ 18 years who provide informed consent meet the inclusion criteria.

#### Exclusion criteria

The exclusion criteria are as follows:Inability to provide informed consentPregnancy or breastfeedingPreoperative left ventricular ejection fraction (LVEF) < 30%Pre-existing renal insufficiency with an estimated glomerular filtration rate (eGFR) < 30 ml/min/1.73 m^2^Postoperative mechanical circulatory support devices such as left ventricular assist device (LVAD), intra-aortic balloon pump (IABP), Impella, or extracorporeal membrane oxygenation (ECMO) devicePre-existing serum sodium level of > 145 mmol/L or < 135 mmol/LPre-existing serum chloraemia > 111 mmol/L or < 96 mmol/LSystemic steroid therapy (at any dose at time of inclusion)Chronic liver disease (bilirubin > 3 mg/dl)Any signs of infection or sepsis defined as clear clinical evidence for active infection or current antibiotic therapy

### Randomisation and blinding

All patients undergoing cardiac surgery and meeting the eligibility criteria as defined above will be enrolled in the study and randomised to either the HS group (7.3% NaCl) or the NS group (0.9% NaCl). Computerised randomisation using a variable block size [2, 4, 6] will be performed by a member of the study team not involved in any part of treatment (neither nurse, resident, nor supervisor). A box with the study vials and study infusion will be given to the treating intensive care physician with the patient’s number in the study. Participants, care providers, investigators, and outcome assessors will be blinded to study group assignment. A list for emergency un-blinding of the study will be held by a designated study quality manager.

### Management of study material

Boxes with the study numbers containing unlabelled infusions will be prepared for all patients prior to study start. One box will contain a 1 × 500 ml + 1 × 100 ml flask of 0.9% NaCl (B. Braun, Sempach, Switzerland) and 20 unlabelled vials of either 0.9% or 23.4% saline (Bichsel, Interlaken, Switzerland). For patients who weigh < 111 kg, 100 ml 0.9% NaCl of the 500-ml 0.9% NaCl flask will be removed by syringe and 16 vials will be added to the remaining 400 ml 0.9% NaCl, to create either a study infusion of 0.9% saline or 7.3% saline.

For patients who weigh > 110 kg, we will prepare a 500-ml 0.9% NaCl flask as described for patients ≤ 110 kg and 1 ×100 ml 0.9% NaCl to which 4 vials of either study infusion are added. All patients will receive 5 ml/kg of the study infusion over 60 min. The weight-adjusted amount of study fluid will be prepared bedside by the treating ICU nurse and given at 5 ml/kg body weight over 60 min via infusion pumps through a central venous line.

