#### Fluid management and haemodynamic protocol in the ICU

On admission to the ICU, patients will receive 5 ml/kg ideal body weight of HS (7.3% NaCl) or NS (0.9% NaCl) by infusion pump for 60 min. Thereafter, ICU treatment will continue according to clinical routine.

If needed, norepinephrine is the first-choice vasopressor and will be titrated to a mean arterial pressure (MAP) judged adequate for the respective patient depending on age and history of hypertension and kidney injury. The range of target MAP is typically between 55 and 65 mmHg. Epinephrine will be added when an additional agent is needed to maintain adequate blood pressure, and if necessary norepinephrine will be exchanged for epinephrine. Dopamine is not used. In the presence of myocardial dysfunction — as suggested by increased cardiac filling pressures and low cardiac output — a dobutamine infusion will be administered. If patients become hypertensive, afterload will be reduced by nitroprusside natrium infusion.

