### Safety measures during study conduct

The infusion of HS can lead to several side effects including electrolyte disturbances (hypernatraemia, hyperchloraemia, hypokalaemia), occurrence of acidosis, and development of oedema. Hence the following safety measures are taken: Before the start of the study intervention, in the ICU a secondary screening will be performed. First, a blood gas analysis will be done before the start of the study intervention to ensure a serum sodium concentration postoperatively below 145 mmol/L and a serum chloride concentration below 107 mmol/L. Second, a doctor of the research team will be contacted if intraoperative complications such as massive bleeding, severe haemodynamic turbulence, or intraoperative myocardial infraction occurred. Based on the blood gas analysis results and/or the medical history, it will be decided if the study is to proceed. Patients admitted from the ICU with cardiac assist devices such as an IABP or an ECMO device or electrolyte levels outside the normal range will be dropped from the study before receiving the study intervention.

If the study is started, a blood gas analysis will be performed 1 h after study infusion termination. For the first 20 patients we will perform a blood gas analysis after 30 min and 60 min of study infusion to check serum sodium levels; thereafter, if the sodium levels stay below 155 mmol/L during infusion of the study fluid, this additional blood gas analysis will be omitted. One hour after termination of the study infusion an additional blood gas analysis will be performed; thereafter, blood gas analyses will be performed every 2 h for the next 6 h and thereafter according to clinical routine.

If the serum sodium level is above 155 mmol/L or the serum chloride level is above 125 mmol/L at any time point, the infusion of the study medication will be stopped.

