### Study parameters

We will obtain baseline data (age, gender, height, weight, BMI), baseline comorbidities, risk scores, and preoperative and postoperative routine laboratory parameters in all patients. Additionally we will perform sonographic assessment of renal blood flow and assess body composition (bioimpedance) at predefined endpoints.

All types of fluids and the cumulative amounts (blood products included), daily body weight, and cumulative doses of medication will be documented. Furthermore, the need for renal replacement therapy, length of mechanical ventilation, length of ICU and hospital stays, and mortality will be assessed.

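### The study infusion is dosed on ideal body weight in two sections and on body weight in the bedside instruction, so a heavy patient's volume and sodium load depend on which section is followed

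*Protocol article*

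**What the plan says.** Three places in the protocol article give the dose.

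- Abstract, Methods: patients are "randomly assigned to receive 5 ml/kg ideal body weight HS (7.3% NaCl) or normal saline (NS, 0.9% NaCl) infused within 60 min".
- Fluid management and haemodynamic protocol in the ICU: "patients will receive 5 ml/kg ideal body weight of HS (7.3% NaCl) or NS (0.9% NaCl) by infusion pump for 60 min".
- Management of study material, which tells the ICU nurse what to prepare: the fluid is "given at 5 ml/kg body weight over 60 min via infusion pumps through a central venous line". The word ideal is absent. The same section makes up more fluid for heavier patients: "For patients who weigh > 110 kg, we will prepare a 500-ml 0.9% NaCl flask", plus a 100-ml flask with 4 further vials.

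The article neither defines ideal body weight nor gives a formula for it, and nothing says which statement governs.

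The section on safety measures requires a blood gas before the infusion "to ensure a serum sodium concentration postoperatively below 145 mmol/L". It stops the infusion if sodium exceeds 155 mmol/L or chloride exceeds 125 mmol/L. Gases at 30 and 60 min are planned for the first 20 patients; after that, "if the sodium levels stay below 155 mmol/L during infusion of the study fluid, this additional blood gas analysis will be omitted".

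**The concern.** The amount of investigational product is a core item of any protocol, and here the article states it in two ways that diverge as body weight rises above ideal. This is not detail left to a fuller document, because the article itself gives both versions.

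The issue is dose definition and safety in the hypertonic arm. A patient well above ideal weight would receive clearly more 7.3% saline under the bedside instruction than the ICU fluid section allows. Once the early gases are dropped, the next scheduled one is 1 h after the infusion ends. The stopping rule then has no planned measurement during the infusion to act on. A reader of the results could also not say which dose was tested, or judge adherence to it.

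**Working it through.** **1. Reproducing the stated 7.3%.** Inputs from Management of study material: 400 ml of 0.9% NaCl, 16 vials of 23.4%, target 7.3%. The vial volume is not stated, so solve for it.
- Vial fluid needed: 400 × (7.3 − 0.9)/(23.4 − 7.3) = 159 ml, or about 10 ml per vial.
- Standard bag with 10-ml vials: (400 × 0.9 + 160 × 23.4)/560 = 7.33%, in 560 ml.
- Second flask: (100 × 0.9 + 40 × 23.4)/140 = 7.33%, in 140 ml.

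**2. Which weight the kit is built for.**
- Standard bag: 560/5 = 112 kg. Both containers: 700/5 = 140 kg.
- The 110-kg split is therefore where a 5 ml/kg dose on actual weight would exhaust the first bag.
- Height for an ideal weight of 110 kg, assuming an ideal BMI of 22–25: √(110/25) = 2.10 m to √(110/22) = 2.24 m. The Devine formula, also an assumption, gives about 2.18 m for men and 2.23 m for women.
- Under ideal-weight dosing the second flask would almost never be needed.

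**3. Size of the dose difference.** The ratio is actual weight/ideal weight, which equals actual BMI/ideal BMI.

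| Actual BMI | Ideal BMI 25 | Ideal BMI 22 |
|---|---|---|
| 25 | 1.00 | 1.14 |
| 30 | 1.20 | 1.36 |
| 35 | 1.40 | 1.59 |

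With Devine, weights of 90–130 kg and heights of 160–185 cm give ratios from 1.13 to 2.48. A 175-cm man of 70 kg shows no material difference (353 versus 350 ml).

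**4. Sodium load, as an illustration.** Sodium content is 73 g/L ÷ 58.44 = 1249 mmol/L. Assume an ideal weight of 70 kg and an actual weight of 91–105 kg, so 350 ml becomes 455–525 ml. Predicted sodium = (Na₀ × TBW + V × 1249)/(TBW + V), with start sodium Na₀ = 144 mmol/L, total body water (TBW) of 40 or 50 L, and no losses.

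| Volume | Sodium given | Predicted, 40 L | Predicted, 50 L |
|---|---|---|---|
| 350 ml | 437 mmol | 153.6 | 151.7 |
| 455 ml | 568 mmol | 156.4 | 154.0 |
| 525 ml | 656 mmol | 158.3 | 155.5 |

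The start sodium at which 155 is reached is (155 × (TBW + V) − V × 1249)/TBW:
- 350 ml: 145.4 (40 L) or 147.3 (50 L), both outside the pre-infusion screen.
- 525 ml: 140.6 (40 L) or 143.5 (50 L), both inside it.

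**5. Primary endpoint.** Inputs from Estimation of sample size and Rationale for effect size: difference 1000 ml, SD 1734 ml, α 0.05, power 80%.
- n per group = 2 × (1.960 + 0.842)² × 1734²/1000² = 47.2, rounded up to 48. The plan's figure reproduces.
- A worst-case half-and-half mix of 350 and 525 ml has an SD of 87.5 ml. The total becomes √(1734² + 87.5²) = 1736 ml (+0.1%), and n remains 48.

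**The case against.** The bedside section never says actual weight. Both places that name a basis say ideal, and one of them is the treatment section, so body weight could be shorthand. The 110-kg rule governs how much is made up, not how much is infused, and a nurse could prepare 560 ml and give less. This reading is possible, but it leaves the second flask without a purpose and the match between 560 ml and 112 kg as a coincidence. The vial volume is inferred, though the stated 7.3% leaves little room for another value.

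The sodium illustration starts near the top of what the screen admits. From 140 mmol/L, 525 ml gives 154.4 (40 L) or 151.5 (50 L), below the limit. Larger patients probably hold more water: at 55 L and a start of 144, 525 ml gives 154.4, again below it. These points stand, and they make the sodium figures illustrative only.

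The safeguards are real. There is a screen before infusion, the early gases test whichever dose is given if practice is consistent, a gas follows 1 h after the infusion, and physicians may order others. But the first 20 patients include only about 10 on hypertonic saline, and whether any were heavy is unknown.

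How many of the 96 patients are affected cannot be told from the document, and differing practice among staff is a risk, not something shown.

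**Conclusion.** The contradiction stands as written and depends on no assumption: two sections dose on ideal body weight, the bedside instruction does not, and its kit is sized for actual weight. Assuming an ideal BMI of 22–25, the dose differs by a factor of 1.20–1.36 at BMI 30 and 1.40–1.59 at BMI 35, and little at normal weight. Reaching 155 mmol/L because of the larger dose is possible within the screening limits, but it depends on start sodium and body water.

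This is a matter of dose definition and sodium safety, not statistical bias. Both arms follow the same ml/kg rule, so the comparison of fluid volume is not distorted and power is not materially changed. It still needs correcting, because the product is concentrated saline and the article describes recruitment as ongoing.

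**What to change.** State one weight basis in the abstract, in Management of study material and in the ICU fluid section. Ideal body weight is the better choice, since it is already the basis in the treatment section and carries the lower sodium load. If it is kept:

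- give the formula; its inputs are already collected ("We will obtain baseline data (age, gender, height, weight, BMI");
- change the bedside instruction to ideal body weight;
- apply the 110-kg kit split to that same weight, accepting that the second flask then becomes practically redundant.

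If actual weight was intended, the other two places must change, and the larger sodium load must be accepted explicitly.

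For patients already treated, record the weight used and the volume infused, and report the delivered dose descriptively by arm. Do not analyse outcomes by delivered ml/kg, because the sodium and chloride stopping rules affect it after randomisation.

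The cost is a wording change in the protocol and the bedside instruction. Weight, height and fluid volumes are already documented, and no extra patients or measurements are needed.

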### Study conduct

Patients included in the trial will receive standard monitoring for cardiac surgical patients in the ICU. We routinely monitor oxygen saturation, heart rate, invasive arterial blood pressure, electrocardiography, temperature, urine output, and central venous pressure.

Echocardiography will be performed preoperatively and intraoperatively. If patients are considered haemodynamically unstable, they receive a pulmonary artery catheter (PAC) according to the hospital’s standard operating procedures (SOPs). Blood gas analysis parameters and mixed venous oxygen saturation will be measured according to clinical routine or as indicated at the discretion of the attending ICU physician.

